### Between group effects

Firstly, it is hypothesised that there will be no significant differences between the scores obtained by the IIG and DIG on the RCADS at T1.Secondly, anxiety scores obtained by the IIG on the RCADS (post intervention) will be significantly lower than the anxiety scores obtained by the DIG on the RCADS at T2.Thirdly, there will be no significant differences in the anxiety scores of the IIG at T2 and DIG on the RCADS at T3.Fourthly, results obtained on the RCADS at post-intervention (T3) will be retained at the three (DIG) and six month (IIG) follow-ups (T4).

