**R = Randomisation**

**X = intervention**

### Participants

It is envisaged that the final sample will consist of approximately 60 children; 30 children in the IIG and 30 children in the DIG who attend Grades 4–7 (aged 9–13 years) at two schools (School 1 and School 2), for children with visual impairments in the Western Cape Province of South Africa. Letters explaining the study will be sent to the two identified schools, and the necessary written consent for participation will be requested from the school principals and school governing bodies.

Parents or guardians of the identified participants (children attending Grades 4–7) will be provided with an information letter explaining the study and a consent form giving their child permission to take part. Identified participants will also be provided with information about the study and they will be required to give written assent before they are delivered the programme. Thus, dual parent-child consent and assent will be required for inclusion. This study received approval (HS888/2013) from the Research Ethics Committee: Human Research (Humaniora) at the Stellenbosch University (Institutional Review Board Number: IRB0005239), and the Western Cape Education Department in South Africa (Reference: 20130507–10635).

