### Participant outcomes

The primary outcome measure in the study relates to changes in levels of symptoms of anxiety and depression on the Revised Child Anxiety and Depression Scale (RCADS) (Chorpita *et al.*
2000). The 30 items of the RCADS assess symptoms across six domains of anxiety and depression in children (aged 6–18), including:

social phobiaseparation anxietyobsessive compulsive disorderpanic disordergeneralised anxiety disordermajor depressive disorder.

Items are rated on a four-point Likert scale. Psychometric properties of the RCADS are good; the six RCADS scales were found to have adequate internal consistency (with all alphas in the .70 and .80 range) and test-retest stability (with one-week test-retest correlation coefficients ranging from .65 to .80) (Chorpita *et al.*
2000; Muris, Meesters & Schouten 2002). The RCADS is freely available on the Internet for download, and permission to translate the questionnaire into Afrikaans was obtained from the authors. Translations were written by a registered clinical psychologist who is fluent in both English and Afrikaans in accordance with the Brislin (1980) back-translation method.

Secondary outcome measures relate to children's worry and self-efficacy measured by the Penn State Worry Questionnaire for Children (PSWQ-C) (Chorpita *et al.*
1997) and Self-Efficacy Questionnaire for Children (SEQ-C) (Muris 2001) respectively. The PSWQ-C (Chorpita *et al.*

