### Statistical analyses

The Statistical Package for the Social Sciences (SPSS) (Van Leeuwen *et al.*
2006) will be used to calculate descriptive and non-parametric statistics. As a result of the envisaged small sample size (*N* = 60), a Mann-Whitney test will be used to determine the significance of differences between the quantitative pre-and-post intervention measures (George & Mallery 2006). Pre-intervention (T1) scores will be analysed to determine the equivalence of the IIG and the DIG, before the intervention and change scores (difference between the pre-and post-intervention scores) for the IIG and DIG will be compared to evaluate change as a result of the intervention programme. Qualitative data will be analysed by means of thematic content analyses.

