### Strengths and limitations

The major strength of this study is that it is the first of its kind, with no studies focussed on anxiety prevention and early intervention programmes for children with visual impairments having been conducted previously. Thus, this research has a novel methodology and it will fill an important gap in the literature by developing and promoting critically needed, specifically tailored anxiety prevention strategies which can be used by children with visual impairments. Expected advantages for participants include:

a reduction in anxiety symptomologyan increase in self-efficacythe acquisition of helpful problem solving skills and coping strategies.

Thus, the programme is aimed at optimising human development and, in this way, contributing to future wellbeing and potentially reducing the prevalence of anxiety in the population of children with visual impairments. Rather unique to the study's design is the qualitative feedback from the participants and facilitators relating to their experience of and satisfaction with the anxiety intervention programme. These qualitative data will provide much-needed information to aid in the understanding of an under-researched problem, namely anxiety experienced by children with visual impairments.

One limitation is the study's small sample size. This is the result of logistical and geographical constraints. South Africa is a large country and schools for children with visual impairments are widely dispersed which, thus, limits the author's capacity to travel to numerous schools on a week-by-week basis.

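### Hypothesis 2 tests the RCADS anxiety score at T2, the analysis section tests the change score, and the article does not say which comparison decides whether the programme worked

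*Protocol article*

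**What the plan says.** Three places in the protocol article bear on the main randomised comparison.

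- **Between group effects, second hypothesis:** "anxiety scores obtained by the IIG on the RCADS (post intervention) will be significantly lower than the anxiety scores obtained by the DIG", at T2. This is a score level at one time point, with no baseline term.
- **Statistical analyses:** "a Mann-Whitney test will be used to determine the significance of differences between the quantitative pre-and-post intervention measures". It goes on: "Pre-intervention (T1) scores will be analysed to determine the equivalence of the IIG and the DIG", and "change scores (difference between the pre-and post-intervention scores) for the IIG and DIG will be compared to evaluate change as a result" of the programme. The tested variable is change, and T1 otherwise serves only as an equivalence check.
- **Participant outcomes:** "The primary outcome measure in the study relates to changes in levels of symptoms of anxiety and depression" on the RCADS. This also points to change.

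The Programme evaluation section introduces the six hypotheses as ones to be tested, so the second is a planned test and not background. The Discussion expects reduced anxiety symptoms in the IIG relative to the DIG, which fits either variable. No section says which comparison is decisive.

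**The concern.** The second hypothesis is the only one of the six that compares treated with untreated randomised children after an intervention. The first concerns T1, the third sets one treated group against the other, the fourth concerns follow-up when both groups have been treated, and the last two are within-group. The causal claim of the trial therefore rests on this contrast.

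A Mann-Whitney test on the T2 score and one on the change score use different data and give different p-values. A team that follows the article faithfully can run both. If only one is significant, the article offers no basis for a conclusion. If the favourable one may be reported, there are two routes to a positive result.

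**Working it through.** **Inputs from the article.** Planned allocation: "30 children in the IIG and 30 children in the DIG". Test: Mann-Whitney. One-week retest correlations for the six RCADS scales: 0.65 to 0.80 (Participant outcomes). Of the small sample size, the limitations section says: "This is the result of logistical and geographical constraints". The article states no power, effect size, SD or alpha, so there is no figure to reproduce.

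**Assumptions, not in the article.** Normal scores, equal SDs at T1 and T2 (set to 1), two-sided alpha 0.05, no dropout, a true T2 difference of 0.5 SD, and change taken from T1 to T2 in both arms. The T1–T2 correlation r is varied from 0.3 to 0.8, because the retest figures are for single scales over one week while the programme alone takes five weeks.

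**Step 1: target.** Randomisation makes the expected T1 difference zero. The expected IIG–DIG difference is therefore the same for the T2 score and for T2 − T1.

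**Step 2: effect of a chance T1 imbalance D.** The T2 contrast shifts by rD. The change contrast shifts by rD − D = −(1 − r)D, which is the opposite direction. With 30 per arm, the standard error of the T1 difference is √(2/30) = 0.258 SD. An imbalance of that size at r = 0.65 moves the T2 contrast by 0.65 × 0.258 = 0.168 SD and the change contrast by −0.35 × 0.258 = −0.090 SD.

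**Step 3: precision.** The SD is 1 for the T2 score, √(2(1 − r)) for change and √(1 − r²) after adjustment for T1. Approximate power is Φ(0.5 / (SD × 0.258) − 1.96).

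- T2 score: Φ(1.936 − 1.96) = 49%.
- Change, r = 0.3: SD 1.183, power 37%.
- Change, r = 0.5: SD 1.000, power 49%.
- Change, r = 0.65: SD 0.837, power 64%.
- Change, r = 0.8: SD 0.632, power 87%.
- Adjusted for T1, r = 0.3, 0.5, 0.65, 0.8: power 53%, 61%, 72%, 90%.

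**Step 4: simulation of the two Mann-Whitney tests** (100,000 trials per setting, 30 per arm).

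| r | Power, T2 score | Power, change | Only one significant (0.5 SD effect) | Either significant (no effect, two-sided) |
|---|---|---|---|---|
| 0.3 | 45.8% | 34.8% | 31.1% | 8.8% |
| 0.5 | 45.8% | 45.5% | 34.3% | 9.0% |
| 0.65 | 45.9% | 60.3% | 38.5% | 9.4% |
| 0.8 | 45.8% | 83.5% | 47.1% | 9.6% |

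**Step 5: direction.** The last column counts results in both directions, whereas the second hypothesis predicts lower scores in the IIG. Counting only false findings of benefit gives about 4.0% to 4.7%, against 2.5% for a single test. Halving the last column gives 4.4% to 4.8%, which agrees closely.

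**The case against.** The best defence is that the Statistical analyses section is the only place that says how the programme is evaluated. On that reading it simply makes the second hypothesis operational. The primary outcome wording agrees with it, and the hypothesis names no test. A condensed article may also leave the choice of deciding comparison to a fuller plan. Much of this is fair, and change is the better-supported reading. It does not remove the conflict: the hypotheses are said to be tested, the second is written on T2 scores, and the article fixes a variable in both places. This is a mismatch, not an omitted detail.

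Four stronger readings are tempting and should be resisted.

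- A reader might infer two different treatment effects. Under randomisation the expected mean difference is the same. What differs is the test, its precision and the realised verdict.
- A reader might infer that the authors mean to claim success on either test. The article does not say so. The error inflation applies only if that were allowed.
- A reader might take 8% to 10% as the rate of false success. That counts the IIG being significantly worse as well. False benefit stays below 5%.
- A reader might take the 31% to 47% as contradictory findings. It means that one test reaches significance and the other does not. Significance in opposite directions occurred in about 0.01% of simulated trials or fewer. Part of the disagreement reflects limited power with 30 per arm.

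The correlation is also weakly informed, so the figures at r = 0.8 are an upper end and not a forecast.

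**Conclusion.** The inconsistency stands: the only randomised treated-versus-untreated comparison is stated on one variable in the hypotheses and on another in the analysis section and the primary outcome, with no rule for which decides. Under the assumptions listed, the choice moves power between about 46% (T2 score) and anywhere from about 35% to 84% (change), with no power difference near r = 0.5. Even there, only one of the two tests is significant in about 34% of trials. Allowing either test would raise the false-benefit rate from 2.5% to about 4.0–4.7% (two-sided, from 5% to between 8% and 10%). These are illustrative ranges and not corrections of a stated figure. They also depend on change meaning T1 to T2 in both arms, which the analysis section does not spell out. The Programme evaluation section gives the immediate pre-post window of the DIG as T2 to T3, and on that reading the change comparison would set treated against treated. The point is worth fixing before analysis.

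**What to change.** Name one deciding between-group comparison and use it in the second hypothesis, the primary outcome and the analysis section.

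- **Preferred:** the IIG–DIG difference in RCADS anxiety score at T2, adjusted for the T1 score, by ANCOVA or by rank-based ANCOVA to keep the non-parametric intent. Under the same assumptions, rank-based ANCOVA has about 48% to 83% power across r = 0.3 to 0.8, which is above or about equal to the better of the two stated tests.
- **Alternative, closer to the current text:** keep the Mann-Whitney test on change, define change as T1 to T2 in both arms, and restate the second hypothesis as a larger T1-to-T2 reduction in the IIG than in the DIG.

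In either case, label the unadjusted T2 comparison descriptive and base no claim of effectiveness on it.

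The cost is a few reworded sentences, with no new data or visits. The authors give up a second route to a significant result, and the preferred option replaces the stated Mann-Whitney test for this comparison.

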## Method

A specifically tailored CBT-based anxiety intervention for South African children with visual impairments will be evaluated in two special schools that cater for children with visual impairments. This study is set up as a randomised wait-list control group design with pre-, post-and follow-up intervention measures, with 60 participants randomly assigned to an IIG (*n* = 30) and a DIG (*n* = 30). Before implementation of the programme 10 participants from each group will be randomly selected to take part in a focus group. The focus group will be aimed at obtaining the participants’ personal inputs and to pilot certain sections of the programme before final implementation. Both of the programme's groups will receive the 10 session anxiety intervention programme**.** The participants will complete baseline (T1), post intervention (T2 for IIG and T3 for DIG) and 3 month (T3 for IIG and T4 for DIG) or 6 month (T4 only for IIG) follow-up assessments.

The research design can be represented as follows:

R  IIG T1   X  IIG T2     IIG T3  IIG T4

R  DIG T1     DIG T2  X  DIG T3   DIG T4

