## Programme evaluation

As mentioned above, all assenting children from School 1 and School 2 will randomly be assigned to 1 of 2 groups at their respective school (an IIG or a DIG). The IIG groups from School 1 and School 2 will be combined to form one large IIG, whilst the DIG groups from School 1 and School 2 will be combined to form one large DIG.

The evaluation phase will comprise both a quantitative and qualitative component (more information about the qualitative component is given below). For the quantitative evaluation, all assenting children in the IIG and DIG (approximately 60 participants) will be administered a short biographical questionnaire (only at T1) and three self-report questionnaires at pre (T1), post (T2), and follow-up (T3 and T4) intervention. Children in the IIG will receive the intervention programme before the children in the DIG. It is envisaged that the programme will be delivered to the two groups (the IIG and DIG) of children according to the following outline:

Initial assessment of all children, IIG and DIG (T1)Children in the IIG receive the anxiety intervention programme (5 weeks)Re-assessment of all children, IIG and DIG (T2)Children in the DIG receive the anxiety intervention programme (5 weeks)Re-assessment of all children, IIG and DIG (T3)Final assessment of all children, IIG and DIG (T4 – It will be 6 months after the children in the IIG received the intervention and 3 months after the children in the DIG received the intervention). Resulting from time constraints, where all assessments should be conducted within one academic year, there will be no 6 month follow-up for the DIG, and no wait period for the IIG.

It will be possible to measure:

The stability of the measures when untreated over time (The DIG will act as a wait-list control group using T1 and T2 comparisons)The impact of the anxiety intervention programme immediately after completion (using immediate pre and post-data from both groups – IIG [T1 and T2]; and DIG [T2 and T3])The maintenance of the effects of the anxiety intervention programme over time following intervention (IIG using T2, T3 [3 month] and T4 [6 month] comparisons, and DIG using T3 and T4 [3 month] comparisons)

The following six hypotheses are to be tested during the evaluation phase of the proposed study (four hypotheses pertain to between group effects and two hypotheses pertain to within group effects).

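### Hypotheses 1 and 3 take a non-significant difference as support for similarity with no margin, and hypothesis 4 starts the IIG's retention at T3 although its post-intervention point is T2

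*Protocol article*

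**What the plan says.** Programme evaluation lists six hypotheses to be tested. Under Between group effects:

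- Hypothesis 1, baseline: "there will be no significant differences between the scores obtained by the IIG and DIG on the RCADS at T1".
- Hypothesis 3, each group just after its own programme: "there will be no significant differences in the anxiety scores of the IIG at T2 and DIG on the RCADS at T3".
- Hypothesis 4, follow-up: "results obtained on the RCADS at post-intervention (T3) will be retained at the three (DIG) and six month (IIG) follow-ups (T4".

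Statistical analyses adds: "Pre-intervention (T1) scores will be analysed to determine the equivalence of the IIG and the DIG". The only test named there is the Mann-Whitney test. No equivalence margin appears anywhere in the article.

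On timing, the Method section places the assessments as "post intervention (T2 for IIG and T3 for DIG". Data collection agrees: T2 comes immediately after the IIG's programme and T3 immediately after the DIG's. Programme evaluation describes the maintenance comparisons as "IIG using T2, T3 [3 month] and T4 [6 month] comparisons, and DIG using T3 and T4 [3 month] comparisons".

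**The concern.** There are two separate problems.

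First, hypotheses 1 and 3 are worded so that they are borne out whenever a difference test fails to reject. A Mann-Whitney test can give evidence of a difference. Its failure to do so is not evidence of similarity unless the interval around the estimate excludes differences that matter. In a small trial, failure to reject is likely even when the groups differ moderately. At T1 there is a further point: allocation is random within schools, so any baseline difference is due to chance, and a significance test of it does not answer whether the groups are equivalent.

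Second, hypothesis 4 uses one reference point, T3, for both groups. That is the post-intervention assessment for the DIG only. In the IIG, T3 is already a follow-up assessment, so a change between T2 and T3 falls outside the hypothesis.

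At stake are statements that the groups were equivalent at baseline, that they scored alike after treatment, or that gains lasted. The first two could rest on the trial being small, and the third on the wrong starting point.

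**Working it through.** **Inputs**

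- Size and allocation, from Method: "with 60 participants randomly assigned to an IIG (*n* = 30) and a DIG (*n* = 30".
- Test, from Statistical analyses: Mann-Whitney.
- Not stated in the article, so assumed here: two-sided alpha 0.05, no dropout, no clustering by school or therapy group, and normally distributed scores in SD units.
- The article gives no power, alpha, SD or margin, and Strengths and limitations attributes the sample size to logistics and geography. There is therefore no figure of the plan's own to reproduce.

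**Precision of a comparison between groups**

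Standard error of the difference = √(2/30) = 0.258 SD. The 95% CI half-width is t(58) × 0.258 = 2.002 × 0.258 = 0.517 SD (0.506 SD with the normal quantile).

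**Chance of a non-significant result when a true difference exists, 30 vs 30**

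| True difference | t-test | Mann-Whitney, efficiency 3/π | Mann-Whitney, 4,000 simulations |
|---|---|---|---|
| 0.3 SD | 79% | 80% | 80% |
| 0.5 SD | 52% | 53% | 55% |

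The difference detectable with 80% power is (1.960 + 0.842) × 0.258 = 0.72 SD, or about 0.74 SD allowing for Mann-Whitney efficiency.

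**What showing similarity would take**

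For two one-sided tests at 0.05 with a true difference of zero (normal approximation), power = 2Φ(m/0.258 − 1.645) − 1 for margin m, set to zero if negative. The number per arm for 80% power is 2 × ((1.645 + 1.282)/m)².

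| Margin | Power at 30 per arm | Needed per arm for 80% |
|---|---|---|
| 0.3 SD | about 0% | 191 |
| 0.4 SD | about 0% | 108 |
| 0.5 SD | 23% | 69 |
| 0.6 SD | 50% | 48 |
| 0.8 SD | 85% | 27 |

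**Hypothesis 4: the sections side by side**

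| Section | IIG post-intervention | IIG retention measured from |
|---|---|---|
| Method | T2 | – |
| Data collection | T2 | – |
| Programme evaluation | T2 | T2, with T3 and T4 |
| Between group effects, hypothesis 4 | T3 | T3 |

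Suppose the IIG mean falls by δ from T1 to T2, rises by δ from T2 to T3, and stays there to T4. The T3-to-T4 change is 0, so hypothesis 4 as worded is met. The T2-to-T4 change is +δ, so the whole gain has been lost.

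**Precision within one group (illustration only)**

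For a paired comparison with n = 30, the SD of change is √(2(1 − r)). A true rebound of 0.3 SD would be non-significant in about 62–64% of trials at r = 0.5, 50–52% at r = 0.65 and 26–29% at r = 0.8 (normal approximation and t-test respectively). These correlations are assumptions. The article's retest coefficients are one-week values for single RCADS scales and do not supply them.

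**The case against.** The strongest reply is that little depends on these hypotheses. Efficacy is judged by hypothesis 2 and by the comparison of change scores, and the Discussion restates only the superiority hypothesis. No later analysis is conditional on the T1 test, baseline tests are common, and the article admits its small sample. Margins and interval reporting can also be left to a fuller plan. Most of this stands and limits the weight of the point. It does not remove it, because the predicted null results and the equivalence wording are in the protocol text itself, and a later analysis plan could not correct them without restating the hypotheses.

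Four stronger readings are tempting, and the article does not support them:

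- **That hypothesis 4 is also to be proved by a non-significant test.** It speaks of results being retained and names no test or criterion. Reading a null test into it is an inference from hypotheses 1 and 3.
- **That relapse in the IIG goes unmeasured.** All children are assessed at all four times, and Programme evaluation plans IIG maintenance comparisons starting at T2. The defect is a contradiction between that plan and the hypothesis.
- **That the article claims equal benefit in both groups.** Hypothesis 3 compares scores at two assessments and says nothing about equal benefit.
- **That a margin would rescue the similarity claim.** At 30 per arm, a rule with a margin of 0.5 SD or less would nearly always return an inconclusive result for hypothesis 3.

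**Conclusion.** The point holds in two limited parts.

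Hypotheses 1 and 3, together with the use of T1 scores to establish equivalence, let a non-significant result stand for similarity without a margin. At 30 per arm such a result is compatible with differences of around half an SD: a true 0.5 SD difference is missed about as often as not, and a 0.3 SD difference about four times in five. These figures rest on the assumptions listed above. Dropout or clustering would make the comparison less precise.

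Hypothesis 4 contradicts the article's own timing for the IIG and, as worded, would call a gain retained that was lost between T2 and T3 and then stayed lost. The data and the planned T2 comparison exist, so this is a matter of reconciling sections.

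The main efficacy comparison is not affected. The correction should be made before the results are written up, but it does not threaten the trial's principal conclusion.

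**What to change.** 1. **Hypothesis 1.** Remove the T1 significance test and the equivalence wording in Statistical analyses. Tabulate T1 scores by arm instead.
2. **Hypothesis 3.** Restate it as the estimated difference between the IIG at T2 and the DIG at T3 with a 95% CI, and state that non-significance will not be read as similarity. If a similarity claim is wanted, fix and justify a margin on the RCADS in advance, accepting the low power shown above.
3. **Hypothesis 4.** Move it to Within group effects and align it with Programme evaluation: IIG from T2 to T4 with T3 shown, DIG from T3 to T4, each as an estimate with a 95% CI.

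The cost is rewording and interval reporting on data already to be collected, with no extra visits or children. The real downside is that statements of no difference and of retained benefit will often become inconclusive, which is what a trial of this size can support.
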